**Methods:**

A three-arm prospective randomized open-label study with a parallel group design will be used. A total of 25 female adolescents with JIA who have pain will be randomized in a ratio of 2:2:1 to one of the 3 groups: (1) online yoga training program (group A: n=10); (2) online aerobic dance training program (group B: n=10); and (3) electronic pamphlet control group (group C: n=5). Participants in groups A and B will complete 3 individual 1-hour sessions per week using online exercise videos, as well as a 1-hour virtual group session per week using a videoconferencing platform for 12 weeks. Participants from all groups will have access to an electronic educational pamphlet on PA for arthritis developed by the Arthritis Society. All participants will also take part in weekly online consultations with a research coordinator and discussions on Facebook with participants from their own group. Feasibility (ie, recruitment rate, self-reported adherence to the interventions, dropout rates, and percentage of missing data), acceptability, and usability of Facebook and the videoconferencing platform will be assessed at the end of the program. Pain intensity, participation in general PA, morning stiffness, functional status, fatigue, self-efficacy, patient global assessment, disease activity, and adverse events will be assessed using self-administered electronic surveys at baseline and then weekly until the end of the 12-week program.

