Create a new Facebook account: All participants will be asked to create an account specifically for the study and select a username that is meaningful to them but does not contain their first or last name, allowing them to remain anonymous.Access the group Facebook page: All participants will be invited to access the link to their group Facebook page, which they will be provided during their group assignment. Participants will be invited to follow the REDCap link provided on the Facebook page and answer baseline questionnaires about their participation in PA, pain, morning stiffness, functional status, fatigue, self-efficacy, and patient global assessment. This will take about 20 to 30 min to complete. The Facebook page will also contain the electronic pamphlet on PA (for all groups), the exercise videos (for groups A and B), and other information.

Following these steps, participants will be asked to complete the training program:

Groups A and B:

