
The following outcome measures will be used to answer the secondary objective:

*Pain intensity* will be assessed using the electronic Childhood Health Assessment Questionnaire (CHAQ) 100-mm pain VAS subscale [65]. It uses a scoring system where 0 mm represents no pain and 100 mm represents very severe pain the past week. This measure has already been validated in the JIA population [65,66]. Pain intensity will be measured at baseline, 6 weeks, and 12 weeks.*Participation in PA (level of PA)* will be assessed by using the electronic Physical Activity Questionnaire for adolescents (PAQ-A) aged 14 to 18 years, a 7-day recall instrument measuring the level of PA within the last 7 days [67-69]. The PAQ-A is composed of 8 items using a 5-point scoring system. The total score is calculated by taking the mean score out of 5, with 1 indicating low PA and 5 indicating high PA. The PAQ-A has been reported to be a valid and reliable measure of general PA levels in youths and adolescents [67-69]. Participation in PA will be measured at baseline, 6 weeks, and 12 weeks.*Participation in PA (duration and intensity)* will be assessed by using an exercise log, based on the 7-day PA Recall calendar [62], which will be used weekly. The PA level will be reported in terms of minutes and intensity levels (3 subscales: moderate, hard, and very hard intensity; subscale total scores in minutes) and will be transformed into the metabolic equivalent of tasks, which are units of the basal metabolic rate and express the energy cost of PA. Participation in PA will be measured at baseline, 6 weeks, and 12 weeks.*Morning stiffness* will be assessed by using electronic self-reported questions asking about the presence (Yes/No) and duration of morning stiffness in minutes. It will be measured at baseline, 6 weeks, and 12 weeks.*Functional status* will be assessed using the electronic CHAQ. The CHAQ contains 8 domains (dressing/grooming, arising, eating, walking, hygiene, reach, grip, and activities), and items are scored using a 4-point Likert scale of 0 to 3, where 0 represents the ability to perform the activity with no difficulty, 1 represents the ability to perform with some difficulty, 2 represents the ability to perform with much difficulty, and 3 represents the inability to perform over the past week. The mean of the 8 scores will determine the total CHAQ score ranging from 0 to 3, with a lower score indicating higher functional status and a higher score indicating lower functional status. It is the most widely used functional health status measure in JIA, which is a reliable and valid tool for the functional, physical, and psychosocial assessment of children with JIA [65]. It will be measured at baseline, 6 weeks, and 12 weeks.*Fatigue* will be assessed by using an electronic version of a subset of the Patient-Reported Outcomes Measurement Information System Pediatric Short Form version 1.0—Fatigue 10a [70], which measures fatigue and its impact, scored from 1 to 5, where 1 represents never tired and 5 represents almost always tired in the past week. It will be measured at baseline, 6 weeks, and 12 weeks.*Self-efficacy* will be assessed by using the Children’s Arthritis Self-Efficacy Scale (CASE), a specific, valid and reliable tool for JIA [71]. CASE is an 11-item self-report scale that is divided into 3 concepts: activity, symptom, and emotion. A 5-point Likert scale is used to rate responses for each item, where 1 represents not at all sure and 5 represents very sure based on the confidence of the child to manage disease effects. It will be measured at baseline, 6 weeks, and 12 weeks.*Patient Global Assessment* will be assessed by using an item used in the Juvenile Arthritis Quality of Life Questionnaire (JAQQ). JAQQ was designed to assess HRQOL in children aged 2 to 18 years JIA or juvenile spondylarthritides [72-75]. JAQQ includes 4 subscales (gross motor function, fine motor function, psychosocial function, and systemic symptoms) as well as a pain and patient global assessment. The patient global assessment asks how youths have been since the last assessment (prior week) on a 5-point Likert scale, scored from 1 to 5, where 1 represents much better and 5 represents much worse. It will be measured at 6 weeks and 12 weeks.*Disease activity* will be assessed by using the active joint count, the number of joints with active disease according to the rheumatologist [1].Adverse events will be reported by participants in answers to open questions.

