
### Data Analysis

Descriptive statistics, such as proportions, means, and standard deviations, will be used to summarize the baseline and end-of-study variables across the 3 study groups (groups A, B, and C) and to assess the distributional assumptions of the statistical techniques used. For the primary objective, data on recruitment rate, randomization process, interventions, clinical and ICT outcome measures, dropout rates, and adherence rates for the interventions will be collected. For the secondary objective, a repeated measures analysis of variance with the fixed-factor study group (A, B, or C) and the within-factor assessment time (0, 6, and 12 weeks) will be conducted to compare groups for the clinical outcome measures at 0, 6, and 12 weeks. An intention-to-treat analysis will be conducted and mixed model repeated measures will be considered to accommodate missing data.

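### The patient global assessment is a change rating with no usable week-0 value and an unsettled recall interval, so the planned 0/6/12-week ANOVA does not fit it; the mode and timing of the joint count also need reconciling

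*Protocol article*

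**What the plan says.** For the secondary objective, Data Analysis plans a repeated measures ANOVA with study group and assessment time as factors, "to compare groups for the clinical outcome measures at 0, 6, and 12 weeks". A mixed model will be considered for missing data. No clinical outcome is exempted.

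Outcome Measures describes the patient global assessment this way: "The patient global assessment asks how youths have been since the last assessment (prior week) on a 5-point Likert scale", scored 1 to 5, "where 1 represents much better and 5 represents much worse". Its schedule there is "It will be measured at 6 weeks and 12 weeks".

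Other sections place the same item differently:
- Methods, Outcomes leaves it out of the baseline list and adds it postintervention.
- Participant Allocation includes it in the questionnaires completed at 6 and 12 weeks. Its baseline steps also ask for "functional status, fatigue, self-efficacy, and patient global assessment".
- The Abstract (Methods) lists it among outcomes that "will be assessed using self-administered electronic surveys at baseline and then weekly until the end of the 12-week program".

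That same Abstract sentence includes disease activity. Outcome Measures defines disease activity as the active joint count, "the number of joints with active disease according to the rheumatologist", and gives no assessment time.

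**The concern.** A 0/6/12-week repeated measures model assumes that the same quantity is measured at all three times and that week 0 is the starting state. A rating of how things have changed does not meet that assumption. Before the programme starts there is no programme-related change to rate, and a rating of recent change at entry says nothing about the level of well-being at entry.

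The recall wording adds a second problem. If the item is asked only at weeks 6 and 12, the last time it was asked and the week just past are different intervals, so two participants with the same course could answer differently depending on which phrase they follow.

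Methods, Outcomes names overall well-being and joint inflammation signs among the essential outcomes for trials in this disease. The section on sample size for the future trial says the pilot will help estimate variance for that trial. A variance from an item whose recall interval is not fixed would be a poor input.

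**Working it through.** **1. Where the global item is scheduled**

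| Place in the article | Baseline | Weekly | Week 6 | Week 12 |
|---|---|---|---|---|
| Outcome Measures | no | no | yes | yes |
| Methods, Outcomes | not listed | not listed | not mentioned | yes |
| Participant Allocation, 6- and 12-week questionnaires | – | – | yes | yes |
| Participant Allocation, weekly questionnaire | – | not listed (activity log, pain and fatigue only) | – | – |
| Participant Allocation, baseline steps | yes | – | – | – |
| Abstract, Methods | yes | yes | yes | yes |

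The item's own definition and two other places agree with a schedule that has no baseline. Two places contradict it.

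**2. Fit to the planned model**

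Inputs: N = 25 participants and G = 3 groups (10 + 10 + 5), with T time levels and complete data assumed.

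Degrees of freedom: time = T − 1; group-by-time = (G − 1)(T − 1); within-subject error = (N − G)(T − 1).

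- As planned, T = 3: time 2; group-by-time 2 × 2 = 4; error 22 × 2 = 44.
- On the Outcome Measures schedule, T = 2: time 1; group-by-time 2 × 1 = 2; error 22 × 1 = 22.

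On that schedule no participant has a 0/6/12 record. A mixed model cannot supply week 0, because it is unobserved for everyone by design rather than missing for some.

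**3. If week 0 is collected**

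Let S(t) be a participant's state at week t and r the recall length. Ignoring the coarseness of the 5-point scale, the item rates D(t) = S(t) − S(t − r). The model's change from week 0 to week 12 is then

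D(12) − D(0) = [S(12) − S(12 − r)] − [S(0) − S(−r)].

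The quantity of interest is S(12) − S(0). The two differ, so a week-0 score makes the model computable but not interpretable.

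**4. What each recall reading captures**

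Suppose, for illustration, that a participant improves by d by week 4 and keeps the gain.

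| Reading | Week-6 rating | Week-12 rating | Programme weeks covered |
|---|---|---|---|
| Prior week, asked at 6 and 12 | S(6) − S(5) = 0 | S(12) − S(11) = 0 | 1 + 1 = 2 of 12 |
| Since last rating, asked at 6 and 12 (week 6 referred to entry) | S(6) − S(0) = d | S(12) − S(6) = 0 | 6 + 6 = 12 of 12 |
| Since study start, asked at 6 and 12 | S(6) − S(0) = d | S(12) − S(0) = d | 12 of 12 |

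The two phrases in the item description coincide only if the item is asked weekly, as in the Abstract. Coverage therefore runs from 2 to 12 of the 12 weeks depending on the reading, and the article does not settle which applies.

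**5. Disease activity**

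- Mode: self-administered survey (Abstract) against a rheumatologist's count (Outcome Measures).
- Time: baseline and weekly (Abstract) against none stated (Outcome Measures).
- Described follow-up at 6 and 12 weeks: online questionnaires (Participant Allocation).
- Described contact with the rheumatologist: the regular visit at which participants are identified (Recruitment).

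The first two lines are direct contradictions. The last two show that the article describes no source for a count at weeks 6 and 12, but they do not show that none exists.

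**The case against.** The best defence has four parts.

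- **Randomised arms can be compared on a change rating without any baseline.** This is correct. The arms remain comparable at weeks 6 and 12, so a reader should not infer that the item yields no 12-week comparison. What fails is the week-0 level and any change from it.
- **The last assessment may mean the last weekly questionnaire, which would be one week earlier.** The article does not say so, but the reading is possible. It would make the two phrases agree, at the price of the prior-week reading, where the week-12 score misses earlier improvement that was maintained.
- **The article is condensed, and a visit schedule may sit in the full protocol.** This stands for the joint count. A reader might infer that there is no examination after baseline and that the count cannot be compared over time. That rests on silence: no time is given for the count at all, and routine visits are not ruled out. For the same reason the article does not support saying that two of the nine listed secondary outcomes cannot be analysed. The contradiction in mode and timing between the Abstract and Outcome Measures does not depend on silence, and it remains.
- **These are secondary outcomes in a small pilot.** This is true, and it limits the weight of the point. It does not make the stated model fit the item.

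**Conclusion.** The point holds for the patient global assessment. By its own definition it is a change item at weeks 6 and 12, and the 0/6/12-week ANOVA does not apply to it: one of three time levels is either absent for everyone or not a baseline status. The schedule is stated inconsistently across the article, and the recall interval is ambiguous on a 6/12-week schedule. The 2-of-12-weeks coverage figure applies only if both that schedule and the prior-week reading govern, so it is one end of a range and not a property of the plan.

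For disease activity, only the conflict over mode and timing is established.

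The conclusion rests on the article's wording alone; it assumes that the Data Analysis sentence covers every listed clinical outcome, since none is excepted. The consequence is confined to secondary outcomes of a 25-participant pilot. The primary feasibility and acceptability aims do not depend on it. It should be corrected, chiefly so that the outcome definition and its variance are usable for the later trial.

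**What to change.** **Patient global assessment**
- Remove it from the baseline set in Participant Allocation and from the baseline-and-weekly list in the Abstract; align Methods, Outcomes with weeks 6 and 12.
- State one recall interval that matches the schedule, for example since the start of the study.
- In Data Analysis, except this item from the 0/6/12 model and compare arms at weeks 6 and 12 as an ordinal outcome with no week-0 term, showing the distribution of responses by arm.

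**Disease activity**
- Reconcile the Abstract with Outcome Measures on who makes the assessment and when.
- Keep the joint count in the 0/6/12 comparison only if counts are made at those times. Otherwise report it descriptively, with the date of each count.

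**Cost.** One item stem, a few schedule statements and one sentence of analysis text. Results states that recruitment and data collection had not started as of May 11, 2020, so on that date no collected data would have been affected. The one downside is that a since-start anchor departs from the source questionnaire, which should be acknowledged when the item is reported.

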### Outcomes

The feasibility of a full trial will be monitored throughout the study (eg*,* randomization, recruitment and retention of participants, data collection, and self-reported adherence). The acceptability of the interventions will be assessed using online questionnaires at the end of the study.

Clinical outcomes will be evaluated at baseline, weekly, and postintervention (at 12 weeks) through the use of online questionnaires in REDCap (Vanderbilt University). At baseline, pain intensity, functional status, fatigue, and self-efficacy will be assessed. Pain intensity and fatigue will be monitored weekly. Finally, all of these outcomes as well as the patient’s global assessment will be assessed postintervention. Outcomes were selected based on a JIA core set of outcomes to assess in trials [59]. Outcomes that were found to be essential include pain, functional status, patients’ overall well-being (global assessment), joint inflammation signs, and adverse events [59]. Other outcomes that were found to be important but not essential include fatigue, joint stiffness, and PA [59]. Other outcomes need more research to be endorsed, such as coping with the illness, which is related to self-efficacy [59].

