Participants will be invited via Facebook and email to attend an individual online consultation with the research coordinator using a videoconferencing platform. During this consultation, participants can ask questions related to their group assignment, voice their concerns, and establish a plan of action. For the remainder of the study duration, participants will be encouraged to attend, when possible, individual 10-minute online consultations weekly. During these consultations, participants can provide their feedback and discuss their use of the PA program as well as facilitators and barriers to participating. Private meetings are less difficult to schedule than group meetings and provide greater privacy. They may also be more motivating and less intimidating for participants who may feel their voice really matters and has an impact.For the study duration, participants will be asked to complete 3 individual exercise sessions as well as 1 virtual group session each week. The links to the videos will be posted on Facebook and sent by email for participants to use for their individual exercise sessions. For group sessions, the videoconferencing platform link will be posted on Facebook and sent to participants via email. Virtual group sessions will help ensure that they perform the exercises that they observe in the video safely and that they do not hurt themselves. They will also be able to see other participants and be seen if they wish, which will be a motivating factor to perform the PA. A schedule of virtual group sessions offered in the morning or afternoon will be posted on the Facebook group page or sent by email.Participants will be asked to record their PA using a validated exercise log [61] as well as their pain intensity and fatigue by completing a brief online questionnaire that regroups valid instruments on a weekly basis. They will be reminded to do so via Facebook, email, and during their online consultations.

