Group C: Participants will be invited via Facebook and email to attend an individual online consultation with the research coordinator using a video-conferencing platform. During this consultation, participants can ask questions related to their group assignment, voice their concerns, and discuss PA in general and their plan for PA in the future. They will also be invited to consult the electronic pamphlet on PA each week. For the remainder of the study duration, participants will be encouraged to attend, when possible, individual weekly 10-min online consultations. During these consultations, participants can discuss their use of PA, as well as facilitators and barriers to participating in PA. Participants will be asked to record their PA using a validated exercise log [61] as well as their pain intensity and fatigue by completing a brief electronic questionnaire that regroups valid instruments on a weekly basis.

Throughout the study, the Facebook pages will provide a means of communication for participants who will be able to share their experiences, post comments on the videos, and ask questions of each other and the research coordinator. Access to Facebook group pages will be restricted to study participants. Adolescents who cannot or do not want (or are not granted parental permission) to access Facebook will be given a link to the CHEO webpage that will contain information related to the study and their group. However, they will not be able to interact (ie*,* leave comments or questions) using this platform.

At 6 and 12 weeks, all participants will be asked to complete online questionnaires about the program that they were allocated to as well as the acceptability of Facebook to deliver PA programs. They will also be asked if they used any other PA during the study. They will also complete online questionnaires assessing their pain intensity, functional status, fatigue, self-efficacy, and well-being (using a patient global assessment). This will take about 20 to 30 minutes to complete.

As a compensation for the time given by participants, they will receive a US $21.40 gift certificate for completing baseline questionnaires and a US $21.40 gift certificate for completing postintervention questionnaires. They will also receive a personalized certificate of participation (community hours for school).

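### The abstract promises weekly adverse-event surveys, but no questionnaire described in the Methods contains an adverse-event item, and the open questions have no form, time point or recall period

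*Protocol article*

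**What the plan says.** The abstract's Methods paragraph gives a schedule: "disease activity, and adverse events will be assessed using self-administered electronic surveys at baseline and then weekly until the end of the 12-week program".

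The body of the article treats adverse events as follows.

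- **Objectives**: adverse events are among the outcomes of the secondary objective, which compares groups A and B with group C.
- **Outcomes**: "Outcomes that were found to be essential include pain, functional status, patients’ overall well-being (global assessment), joint inflammation signs, and adverse events". The same section says "Pain intensity and fatigue will be monitored weekly" and names no other outcome as weekly.
- **Participant Allocation, weekly record**: groups A and B complete the exercise log "as well as their pain intensity and fatigue by completing a brief online questionnaire that regroups valid instruments on a weekly basis". Group C is described in nearly the same words: "as well as their pain intensity and fatigue by completing a brief electronic questionnaire that regroups valid instruments on a weekly basis".
- **Participant Allocation, baseline and later questionnaires**: the baseline list runs from physical activity to patient global assessment. The later list opens with "At 6 and 12 weeks, all participants will be asked to complete online questionnaires about the program" and goes on to Facebook acceptability, other physical activity, pain, function, fatigue, self-efficacy and well-being. Neither mentions adverse events.
- **Outcome Measures**: "Adverse events will be reported by participants in answers to open questions". Nothing is added about form or timing.

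**The concern.** A coordinator who builds the forms from the Methods would have no instruction to ask about harms weekly, while a reader of the abstract would believe that this was done. The two accounts lead to different data.

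This matters because harms are part of what the pilot is meant to report. Participants enter with arthritis pain of at least 30 on a 100-mm scale. Most of the exercise is done alone from a recorded session. Participant Allocation itself gives preventing injury as a reason for the group sessions, and the Challenges section says that a live instructor would have been ideal. If events are asked about only at the end, or on no fixed occasion, the count depends on what a participant remembers or chooses to mention, and a low count could not be read as evidence of few harms.

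**Working it through.** The plan states no figure on this point, so there is nothing to reproduce. The check is a comparison of the places that fix questionnaire content or timing.

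| Place | What it fixes | Adverse events? |
|---|---|---|
| Abstract, Methods | electronic survey at baseline, then weekly to week 12 | yes, weekly |
| Outcomes | weekly monitoring | no: pain and fatigue only |
| Participant Allocation, baseline | questionnaire list | not listed |
| Participant Allocation, weekly (A and B) | exercise log, pain, fatigue | not listed |
| Participant Allocation, weekly (C) | exercise log, pain, fatigue | not listed |
| Participant Allocation, 6 and 12 weeks | questionnaire list | not listed |
| Outcome Measures | open questions | yes, but no form, time point or recall period |

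In the secondary list under Outcome Measures, every outcome except disease activity and adverse events has time points.

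**Can the abstract's schedule simply be taken as governing?** No. The same sentence of the abstract puts functional status and self-efficacy on the weekly schedule, while Outcome Measures sets them at baseline, 6 and 12 weeks. It also has disease activity self-reported by survey, while Outcome Measures uses the rheumatologist's active joint count. The sentence is unreliable for other outcomes, so it cannot settle this one.

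**Share of exercise done individually** (Interventions, Groups A and B): 3 individual sessions × 12 weeks = 36, and 1 group session × 12 weeks = 12. The total is 48, and 36/48 = 75%.

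**What incomplete capture could do (illustration only).** The documents give neither an event risk nor a capture share, so both are assumed. With n = 20 in groups A and B together, risk p per participant and capture share c, the chance of recording at least one event is 1 − (1 − p·c)^20.

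| Assumed p | c = 1 | c = 0.5 |
|---|---|---|
| 5% | 1 − 0.95^20 = 64% | 1 − 0.975^20 = 40% |
| 10% | 1 − 0.90^20 = 88% | 1 − 0.95^20 = 64% |
| 20% | 1 − 0.80^20 = 99% | 1 − 0.90^20 = 88% |

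These figures show the direction and possible scale of a loss. They do not estimate the loss in this trial.

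**The case against.** **The lists are incomplete, so absence from them proves little.** This is partly right. The 6- and 12-week list under Participant Allocation also omits morning stiffness and the PAQ-A, which Outcome Measures schedules at those visits. The baseline list under Outcomes is shorter than the one under Participant Allocation. The weekly form is described as a set of valid instruments, and an open question is not one. So it cannot be said that the forms will lack the item, only that no section says they have it.

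**The abstract and Outcome Measures are compatible.** A weekly survey with an open question would satisfy both. That is true of those two places alone. It does not dispose of the statement under Outcomes that pain and fatigue are what is monitored weekly, or of the weekly form as described for each arm.

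**Other routes exist.** The feasibility form records dropouts and protocol deviations, with reasons, throughout. This could catch harms that interrupt exercise, but not the others.

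**A weekly item would collect noise.** This stands for a broadly worded item. If 5%, 10% or 20% of participants answered yes in any week (assumed, with independent weeks), 1 − 0.95^12 = 46%, 1 − 0.90^12 = 72% or 1 − 0.80^12 = 93% would have an event by week 12. The question should therefore not ask about any worsening of joint symptoms.

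**A stronger reading that the documents do not support.** Because only groups A and B have weekly group sessions, a reader might infer that events will be captured unequally between arms. That would require events to be gathered at live contacts, and no section names consultations or group sessions as a source. Outcome Measures promises the same questionnaire link and reminders to all groups, and consultations are offered on the same terms in all arms. Unequal capture is at most a possibility.

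**Conclusion.** The inconsistency is in the text and is more than detail left to a fuller protocol, because the article both states a weekly schedule and describes the weekly form without the item. The conclusion is limited: if the Methods are followed as written, weekly elicitation of harms may not happen, for an outcome that the protocol calls essential and compares with group C.

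The size of any under-count cannot be derived from the documents. The primary feasibility and acceptability aims are not affected. The point should be settled before recruitment, which according to the Results section had not started in May 2020. It rests on the assumption that the forms will be built from the Methods. If the full protocol already places the question on the weekly form in every arm, only the wording of the article needs correcting.

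**What to change.** 1. Put one adverse-event question on the existing weekly REDCap form, worded identically in all three arms, with a past-week recall period: any injury or new health problem, yes or no. If yes, record the date and whether it occurred during a study session, then ask the open question as follow-up.
2. Report participants with any event by arm from this form. Show events that occurred during or are related to study sessions separately from other events. List events learned by other routes apart from these.
3. Align the abstract, Outcomes, Participant Allocation (baseline, weekly, and 6- and 12-week lists) and Outcome Measures on which form asks and when. Reconcile the abstract's weekly schedule for the other outcomes at the same time.

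The cost is one more question per week on a form that participants already complete. More minor events and some ordinary disease fluctuation will be recorded, which is why session-related events need their own line.
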